### 5.3 Secondary analyses

- Continuous secondary outcomes analyzed using paired *t*-tests and between-group comparisons of change scores.
- Longitudinal analyses across baseline, 1/2, 3, and 6 months using **linear mixed-effects models**, with fixed effects for group, time, and interaction, and random intercepts for subjects.
- Proportions above/below clinical cut-offs analyzed using  **$\chi^2$  tests**.
- Reliable and clinically significant change indices calculated.

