#### RCT

This study is a population based randomized controlled clinical superiority trial. Participants are randomized to internet-based, TG-iConquerFear or augmented TAU (1:1), see Fig. 1. All participants will follow the standard cancer follow-up program.

Fig. 1, Trial design

[figure not shown]

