### Process of participation

1. Receives “Følgebrev” and a survey (Spørgeskemaer, bilag 1 – screening) in E-boks.
2. Answers. Or reminded after 2 weeks
3. In case of FCRI under 22: No further participation
4. In case of FCRI at or above 22:
  - Informed of elevated level directly in the questionnaire
  - Asked if interested in hearing more about the RCT targeting FCR
  - Asked to enter phone number
  - Asked to fill out another questionnaire (45 items)
5. Telephoned by a research assistant, oral information about RCT is given (purpose, risks, benefits, voluntariness). Rescheduling in case of needing assessor.

6. Semistructured interview is performed by telephone. If possible at the same time as oral information is given, otherwise rescheduled.
7. In case of eligibility and wish to participate: Written information about RCT "Deltagerinformation", consent form "Samtykkeerklæring til projektdeltagelse" and "Før du beslutter dig"-pamphlet is send to E-boks
8. Consenting with Nem-id. Or reminded after 2 weeks of consideration.
9. No answer in 4 weeks is interpreted as not wanting to participate.
10. If consent is given: Randomization
11. Information letter "Informationsbrev" to E-boks, either with link to livogkraeft.rm.dk (control arm) or link to TG-iConquerFear (intervention arm)
12. Control arm or intervention arm for 10 weeks (Spørgeskemaer, bilag 3 – mediationsparametre)
13. 12 weeks after consent form is signed: 1st follow-up (Spørgeskemaer, bilag 4 – follow-up)
14. 12 weeks after 1st follow-up: 2nd follow-up
15. 12 weeks after 2nd follow-up: 3rd follow-up
16. 24 weeks after 3rd follow-up (One year after consent form is signed): 4th and final follow-up

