## EVALUATION

### Primary outcome measure

The primary outcome measure is the 3 month follow-up (T1) total score on the recently validated Danish version of the FCRI [13]. The FCRI is a 42-item self-report measure that includes subscales assessing FCR triggers, severity, psychological distress, functioning impairments, insight, reassurance, and coping strategies [48]. The FCRI has demonstrated high: internal consistency ( $\alpha=0.96$ ) [49], interclass correlation (0.84) [13] and convergent validity in large heterogeneous cancer survivor samples. Respondents rate the degree to which symptoms/issues affected them over the past month on a Likert scale ranging from 0 ('not at all' or 'never') to 4 ('a great deal' or 'all the time'). While there are potential issues with aggregating FCRI subscales [50], total FCRI score will be used as the dependent variable, as it closely reflects proposed features of clinically significant FCR; namely related distress, functional impact, and maladaptive coping[2], rather than the level of fear indicated by the FCRI-SF [50, 51]. Total scores can range from 0-168; higher scores indicate greater FCR morbidity. Level of FCR will be measured post-treatment (T0) and at follow-up after 3 (T1) and 6 (T2) months. Long-term effect will be evaluated after one year (T3). All electronic questionnaires will be sent out automatically through RedCAP.

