### Statistical analysis

A flowchart of participants and dropouts following the CONSORT guidelines will be drawn.

STATA will be used for all statistical analyses. All statistical tests will be two-sided (level of significance = 0.05).  $\chi^2$ -tests will be performed on all follow-up data to analyse proportions of participants above or below the clinical cut-off.

The influence of the intervention will be analysed for the primary outcome and for all secondary outcomes. Linear mixed effects models will be used to analyse longitudinal differences between intervention and control group. Association with functional disorders (health anxiety and bodily distress symptom) and psychiatric disorders (anxiety and depression) will be evaluated with adjusted and unadjusted linear regressions analyses on baseline data.

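### The random-intercept-only mixed model in SAP 5.3 can over-reject for late-visit or slope contrasts if correlation between visits decays; only the secondary longitudinal analyses are affected

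*Combined protocol and SAP*

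**What the plan says.** The protocol, under Statistical analysis, is general: "Linear mixed effects models will be used to analyse longitudinal differences between intervention and control group". It gives no covariance structure. SAP 5.3 gives one: "Longitudinal analyses across baseline, 1/2, 3, and 6 months using" linear mixed models, "with fixed effects for group, time, and interaction, and random intercepts for subjects". Neither document mentions a random slope, a residual correlation structure, robust standard errors, a degrees-of-freedom method or a sensitivity analysis for this model. The SAP does not say whether time is a factor or a linear term.

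On timing, the protocol's Primary outcome measure section states "Level of FCR will be measured post-treatment (T0) and at follow-up after 3 (T1) and 6 (T2) months". Process of participation puts the first follow-up "12 weeks after consent form is signed", the second 12 weeks later, and then "12 weeks after 2 nd follow-up: 3 rd follow-up". The four visits in the model are therefore at about 0, 12, 24 and 36 weeks. The SAP's labels of 1/2, 3 and 6 months are best read as time since the 10-week intervention ended.

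The test level is fixed: "All statistical tests will be two-sided (level of significance = 0.05"). The primary analysis in SAP 5.2 is a two-sample t-test on change scores. SAP 5.3 also specifies between-group comparisons of change scores for continuous secondary outcomes. SAP 7 treats secondary and exploratory analyses as hypothesis-generating.

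**The concern.** A random intercept with a single residual variance forces compound symmetry: baseline is taken to be as strongly correlated with week 36 as with week 12. If correlation weakens with distance, or participants follow individual trajectories, some of that within-person variation is counted as evidence of a group-by-time effect. Contrasts between distant visits get standard errors that are too small, and contrasts between neighbouring visits get ones that are too large. Entry at an FCRI-SF of 22 or more adds a second departure, because selection tends to reduce the variance at baseline and weaken its correlation with later visits.

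This model is the only SAP analysis that uses all four visits jointly. With no imputation planned (SAP 6), it is also the one that uses incomplete records. Statements about the course over time or a sustained effect would naturally draw on it, and its P values and intervals may not have the stated 5% level.

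**Working it through.** **Inputs from the documents.** Four visits at about 0, 12, 24 and 36 weeks (SAP 5.3; Process of participation). Two-sided 5% level (protocol and SAP 8). 1:1 allocation (protocol, RCT). Revised sample 68 with 20% dropout (SAP, September 2023 update), so 68 × 0.8 = 54.4, or about 27 per arm.

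**Input not in the documents.** The correlations between visits. The only related figure is 0.84 for the FCRI, under Primary outcome measure. It is given as a measurement property, not as a correlation between trial visits. All patterns below are assumptions.

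**Formula.** With balanced data and unit variances, the random-intercept fit uses one within-subject variance, 1 − r̄, where r̄ is the mean of the six pairwise correlations.
- Change from baseline at lag k: true/assumed variance ratio V = (1 − r_k)/(1 − r̄).
- Linear slope, scores −3, −1, 1, 3: V = [20 + 2(5r₁ − 6r₂ − 9r₃)]/[20(1 − r̄)].
- Type I error = 2[1 − Φ(1.96/√V)]. Model interval width relative to the correct one = 1/√V.

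**Check at the nominal level.** With all correlations equal, V = 1 for every contrast and the error is exactly 5.0%. The SAP's model is right in that case.

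**Worked example, mild decay 0.70, 0.65, 0.60.** r̄ = (3 × 0.70 + 2 × 0.65 + 0.60)/6 = 0.667, so 1 − r̄ = 0.333. At 6 months V = 0.40/0.333 = 1.20, and the error is 7.4%. For the slope V = [20 + 2(3.5 − 3.9 − 5.4)]/6.667 = 1.26, and the error is 8.1%. Post-treatment V = 0.30/0.333 = 0.90, so the interval is 5% too wide.

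| Assumed correlation at lags 1, 2, 3 | 1 − r̄ | 6-month V | 6-month error | Slope V | Slope error | Post-treatment interval width |
|---|---|---|---|---|---|---|
| 0.60, 0.60, 0.60 | 0.400 | 1.00 | 5.0% | 1.00 | 5.0% | 1.00 |
| 0.70, 0.67, 0.65 | 0.318 | 1.10 | 6.2% | 1.14 | 6.6% | 1.03 |
| 0.70, 0.65, 0.60 | 0.333 | 1.20 | 7.4% | 1.26 | 8.1% | 1.05 |
| 0.714, 0.607, 0.516 (0.84 × 0.85^lag) | 0.355 | 1.36 | 9.3% | 1.49 | 10.8% | 1.11 |
| AR(1) 0.5 | 0.646 | 1.35 | 9.2% | 1.53 | 11.3% | 1.14 |
| AR(1) 0.7 | 0.430 | 1.53 | 11.3% | 1.74 | 13.7% | 1.20 |
| AR(1) 0.84 | 0.246 | 1.66 | 12.8% | 1.88 | 15.3% | 1.24 |

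The 6-month columns apply if time is categorical, the slope columns if it is linear. Both cannot describe the same fitted model.

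**Joint 3-df interaction test** (categorical time). From the weighted chi-square mixture, the error is 5.1% under the 0.70, 0.65, 0.60 pattern, 5.7% under AR(1) 0.5, 6.2% under AR(1) 0.7 and 6.8% under AR(1) 0.9. A simulation of AR(1) 0.84 with 27 per arm gave 7.2%.

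**Effect of baseline selection.** Suppose correlations with baseline are 0.4 and those among follow-ups 0.7. Then r̄ = (3 × 0.4 + 3 × 0.7)/6 = 0.55 and V = 0.60/0.45 = 1.33 at every follow-up. The error is 9.0%, and the post-treatment interval is now too narrow (width 0.87). With baseline correlations of 0.50, 0.45 and 0.40, and 0.70 to 0.75 among follow-ups, the post-treatment error is 7.7% and the 6-month error 10.6%. A smaller baseline variance alone works the other way: equal correlation 0.6 with baseline SD at 0.7 of the follow-up SD gives 3.9% for each change from baseline.

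**Simulation with dropout** (REML fit, AR(1) 0.7, no arm effect, 2,500 runs). With 34 per arm and 20% dropout: 6-month 11.0%, slope 12.8%, post-treatment 2.0%, joint test 6.0%. With 175 per arm and 30% dropout: 11.4%, 13.4%, 2.0% and 5.4%. A larger sample does not remove the problem.

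**After the change.** In complete-data simulations an unstructured covariance gave 4.4 to 5.6% in every scenario. In the dropout simulations, t-tests on each participant's change or slope (equivalent for complete data) gave 4.3 to 5.3% at 6 months and 4.2 to 5.1% for the slope.

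**The case against.** The strongest reply is that little depends on this model. SAP 5.2 assigns the primary comparison to a t-test. The change-score comparisons in SAP 5.3 assume no covariance structure and, for complete data, match what an unstructured model would give. Secondary results are declared hypothesis-generating. All of this stands and limits the reach of the point. One gap remains: the SAP does not say outright that 6-month FCRI change gets its own t-test.

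The size can also be challenged, fairly. The largest figures come from pure serial decay, and AR(1) at 0.84 borrows a measurement property as a between-visit correlation. Milder patterns give about 1.5 times nominal or less.

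Three stronger readings are tempting, and the documents do not support them:
- **That the primary result is compromised.** The protocol mentions mixed models just after naming the primary and secondary outcomes, so a reader might infer this. The more specific SAP 5.2 uses a t-test, and the protocol sentence gives no random-effects structure.
- **That the group-by-time test as such rejects two to three times too often.** With categorical time the joint test is close to nominal. The larger figures belong to single contrasts, or to a linear coding the SAP does not state.
- **That the post-treatment interval is simply too wide.** That follows from serial decay, but the direction reverses if selection weakens the baseline correlations.

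Finally, the January 2025 update reports in the past tense which analyses were not done. The mixed model is not on that list, so it may already have been run, and a change now would be post hoc.

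**Conclusion.** The point holds in a limited form. SAP 5.3 states a covariance assumption that is doubtful for visits spread over about 36 weeks in a sample selected at baseline, and nothing else in the documents relaxes it. Over the decay patterns from 0.70, 0.65, 0.60 to AR(1) 0.84, type I error is 7.4 to 12.8% for the 6-month contrast (categorical time) or 8.1 to 15.3% for the slope (linear time). That is roughly 1.5 to 3 times the nominal 5%, and it shrinks towards 5% as the correlations become equal. The joint 3-df test is only slightly affected. The post-treatment interval is miscalibrated in a direction that depends on the true pattern.

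These figures rest on assumed correlations, equal 12-week spacing and, apart from the baseline-SD check, equal variances. The consequence is confined to the secondary longitudinal mixed-model contrasts; the primary 3-month t-test and the change-score t-tests are untouched. The change is worth making because it is specific and cheap, not because the main conclusion depends on it.

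**What to change.** In SAP 5.3, replace the random-intercept specification with visit as a categorical factor, group, their interaction, and an unstructured within-subject residual covariance across the four visits. Fit by REML with small-sample degrees of freedom such as Kenward-Roger. Report the arm differences at post-treatment, 3 months and 6 months as named contrasts. If the model does not converge, use participant-clustered robust standard errors or add a random slope. If the planned model has already been fitted, keep it and report this one beside it as a labelled sensitivity analysis.

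The cost is a short change of wording and one further model specification, with no new data. An unstructured covariance for four visits has 4 variances and 6 covariances, 10 parameters against 2 in the stated model. The 8 extra parameters should be estimable with about 54 participants.

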### 5.4 Per-protocol analyses

- Primary and secondary outcomes re-analyzed in the PP population to assess consistency with ITT results.

### 5.5 Exploratory analyses

- **Adherence/engagement:** descriptive statistics of modules completed, skew assessed, medians and IQR reported.
- **Dropout analysis:** logistic regression comparing demographic and psychosocial predictors of dropout vs retention.
- **Process measures:** regression models to examine mediators (illness uncertainty, perceived risk, negative beliefs about worry).
- **Associations with functional disorders:** logistic regression for dichotomized outcomes (eg, anxiety, depression, bodily distress) using established cut-offs.

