A diagnosis of cancer is life changing and imposes heavy stress on patient and relatives. Together with often numerous physical symptoms and social changes after the cancer treatment, the net sum of stressors may exceed the cancer survivor's ability to adapt. This overload may manifest as a functional disorder/somatic symptom disorder such as bodily distress syndrome or health anxiety, as proposed by Simonelli et al [18]. Bodily distress syndrome is defined as a condition in which the patient suffers from, usually multiple, bodily symptoms in a characteristic symptom and illness pattern that are not attributable to verifiable, conventionally defined diseases [19].

Health anxiety is characterized by preoccupation with fear of having a serious and life-threatening illness with no objective sign of disease, and preoccupation persists despite medical reassurance [20]. Health anxiety and FCR obviously overlaps, as they also both include unpleasant thoughts or ruminations, which interfere with everyday life and may lead to further unnecessary investigations and treatment. One study investigated hypochondriasis (the cousin of health anxiety) in breast cancer survivors and found that 43 % of those with clinical level of FCR met the diagnostic criteria [21]. Two studies of CRC patients have measured somatization, but not FCR [22, 23]. To the best of our knowledge, no previous studies have investigated the role of functional disorders in relation to FCR, anxiety and depression in CRC survivors.

Illness uncertainty has been linked with FCR [7] and health anxiety [24]. Illness uncertainty might be even greater when diagnosed asymptomatic as a consequence of screening. We postulate that screened to diagnosis leads to increased issues in coping with the cancer and the fear of recurrence. The comprehensive Danish Clinical Registries contain data on the method of diagnosis, e.g. if the CRC survivor is identified through the Danish Nation-wide Colorectal Cancer Screening Program, as opposed to a survivor initially diagnosed as a result of symptoms. This enables research in this unexplored area of psychosocial consequences of screen-detected cancers.

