## AIM

The primary aim of this randomized controlled trial (RCT) is to test if a therapist-guided version of iConquerFear (TG-iConquerFear) can reduce FCR and improve QoL for CRC survivors more than augmented treatment as usual (augmented TAU).

Secondary objectives are to i) outline the prevalence of FCR in a population based CRC cohort up to 5 years post-diagnosis using a validated FCR measure with a clinical cut-off. This comprehensive screening will be used as recruitment for the RCT; ii) Investigate whether being diagnosed as a consequence of the Danish Nation-wide Colorectal Cancer Screening Program increases FCR compared to being diagnosed as a consequence of physical symptoms; and iii) investigate whether FCR is associated with anxiety, depression, bodily distress syndrome and health anxiety in CRC survivors as well as investigate whether uncertainty in illness, negative beliefs about worry and perceived risk of cancer recurrence act as moderators or mediators of FCR.

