### Study population

All Danish CRC survivors above age 18 diagnosed after implementation of the CRC screening programme in March 2014 who have completed curative-intent cancer treatment with surgery and/or radiation and/or adjuvant chemotherapy will be invited to participate in the survey. Estimated number is 15,000 as the incidence is 5,000, and 80 % are offered curative intent treatment. One-year survival rate (data from 2011-2015) is 85 %. 5-year survival rate is 65 %. Overall survival rate used for this estimation is 75 %.

The RCT participants are recruited among the 15,000 colorectal cancer survivors invited to take part in survey. Through cooperation with the Danish Cancer Society we expect a slightly higher response rate than previous reported [43] of 60 %.

Among those 9,000, 12 % (1,080) are expected to score 22 or above on the FCRI-SF [13].

Approximately half of those are expected to be willing to participate in a randomised trial[37], resulting in 540 eligible participants.

The survivors will be identified through the Danish Colorectal Cancer Group (DCCG) database hosted by The Danish Clinical Registries (RKKP) with no need to enter individual patient records. The registry does not contain data on recurrence, and the cover letter will need to explain carefully, that in case of disease recurrence, the participants are asked to notify us in the first question or simply ignore the inquiry from us (see appendix 2. Følgebrev).

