## 1. Background and objectives

This SAP pertains to the randomized controlled trial evaluating the therapist-guided eHealth intervention TG-iConquerFear versus an augmented self-help control for reducing fear of cancer recurrence (FCR) in colorectal cancer survivors.

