### Exploratory outcomes

- Dropout patterns (demographic and psychosocial predictors of attrition).
- Process measures (eg, illness uncertainty, perceived risk of recurrence, negative beliefs about worry) as potential mediators.
- Associations with functional somatic and psychiatric disorders (using validated cut-offs).

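### Protocol and SAP specify different models for the association of fear of recurrence with anxiety, depression, bodily distress and health anxiety; at trial size the SAP's dichotomised model loses precision

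*Combined protocol and SAP*

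**What the plan says.** - **Protocol, Aim, objective (iii):** the study is to "investigate whether FCR is associated with anxiety, depression, bodily distress syndrome and health anxiety in CRC survivors".
- **Protocol, Statistical analysis:** the association with functional disorders (health anxiety, bodily distress) and psychiatric disorders (anxiety, depression) "will be evaluated with adjusted and unadjusted linear regressions analyses on baseline data". The sentence names no dependent variable and does not say how the disorder measures are scored.
- **SAP section 4, Exploratory outcomes:** the same topic is listed as cut-off based.
- **SAP 5.5:** the method is "logistic regression for dichotomized outcomes (eg, anxiety, depression, bodily distress) using established cut-offs". No cut-off value, time point, covariate set or reason for the change is given.
- **SAP section 1:** "This SAP pertains to the randomized controlled trial evaluating the therapist-guided eHealth intervention TG-iConquerFear versus an augmented self-help control". The survey cohort is not mentioned.
- **SAP, September 2023 update:** the trial target becomes 68 participants.
- **SAP, January 2025 update:** the deviations listed are the per-protocol, mediator, predictor and economic analyses. The association analysis is not among them, so it still stands.

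**The concern.** One question has two models, and nothing tells the analyst or the reader which governs. The two can give different answers: one yields a slope, the other an odds ratio for being above a threshold.

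The SAP model is also the less precise. The protocol's survey procedure collects SCL4-anx, SCL6-dep, the BDS checklist and Whiteley-8 as multi-item scales. A cut-off treats a person just above it like the most severe case, and a person just below it like someone with no symptoms. In a sample of trial size, a moderate association could be missed or reported with a wide interval.

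The SAP version also leaves a choice open. The only clinical cut-off with a value in the documents is 22 on the FCRI-SF. None is given for the four scales to be dichotomised.

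**Working it through.** The plan gives no sample size, power or efficiency for this analysis, so there is no figure of its own to reproduce.

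**1. The two texts side by side**

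| | Protocol | SAP |
|---|---|---|
| Model | linear | logistic |
| Dependent variable | not named; must be continuous | disorder measure, dichotomised |
| Adjustment | with and without | not stated |
| Data | baseline | time point not stated |
| Population | not stated in the sentence | trial |

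If the protocol's dependent variable was the FCRI score, the SAP has exchanged outcome and predictor as well as changed the model.

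**2. Information lost by a cut-off**

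Assumptions: normal score, weak association, proportion p above the cut-off. Relative efficiency = φ(z)² / [p(1 − p)], where z is the normal quantile for p.

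- p = 0.5: 0.3989² / 0.25 = 0.637, loss 36.3%
- p = 0.3: 0.576, loss 42.4%
- p = 0.2: 0.490, loss 51.0%
- p = 0.1: 0.1755² / 0.09 = 0.342, loss 65.8%
- p = 0.05: 0.224, loss 77.6%

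The sample size needed for equal precision rises by 1/0.637 = 1.57 to 1/0.342 = 2.92 over p = 50% to 10%.

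The documents do not supply p for these scales. Two nearby figures do not fit. One study in breast cancer survivors "found that 43 % of those with clinical level of FCR met the diagnostic criteria", but for hypochondriasis. The statement that "12 % (1,080) are expected to score 22 or above on the FCRI-SF" concerns FCR itself.

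**3. Sensitivity to the normal assumption**

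Simulated samples of 200,000, comparing squared Wald statistics from linear and logistic fits. The correlation is that of the underlying normal variables. Losses are for 50% / 25% / 10% above the cut-off.

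| Score | Correlation 0.1 | Correlation 0.3 |
|---|---|---|
| Normal | 34 / 48 / 66% | 46 / 53 / 71% |
| Gamma, shape 1 | 23 / 30 / 57% | 32 / 43 / 63% |
| Gamma, shape 0.5 | 5 / 21 / 53% | 19 / 31 / 55% |

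Skewness reduces the loss, most of all when the cut-off is near the median.

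**4. Effect on power**

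Power ≈ Φ[atanh(r)·√(m − 3) − 1.96], where m is n times the efficiency in step 2. For n = 68 and r = 0.3, atanh(r) = 0.3095:

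- continuous, m = 68: 0.3095 × 8.062 − 1.96 = 0.535, power 70%
- p = 50%, m = 43.3: 0.3095 × 6.349 − 1.96 = 0.005, power 50%
- p = 10%, m = 23.3: 0.3095 × 4.501 − 1.96 = −0.567, power about 29%

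A separate simulation (1,000 samples per cell, likelihood-ratio test for the logistic model) gave about 70% for linear, and about 50%, 50%, 40% and 30% for logistic at p = 50%, 30%, 20% and 10%.

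Other sizes, as continuous / p = 50% / p = 10%:

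- n = 246, r = 0.2: 88 / 71 / 45%
- n = 9,000, r = 0.1: about 100% throughout
- n = 9,000, r = 0.05: 99.7 / 96.6 / 79.2%

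The correlations are assumptions. Every trial participant must score at least 22 on the FCRI at entry, which narrows the FCR range. The value of r is therefore the one within that selected group, and bivariate normality is only approximate.

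**The case against.** The strongest reply is that this is an exploratory analysis with a legitimate target of its own. The question is framed around disorders, and whether FCR goes with being a likely case is a fair thing to ask. SAP section 7 treats secondary and exploratory results as hypothesis-generating. This stands, and it is why the cut-off analysis should be kept as supplementary and why the priority is modest.

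A reader might also draw stronger conclusions that the documents do not support:

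- *That the protocol analyses the four conditions as continuous scores.* This is an inference. A linear model with FCRI as dependent variable and case status as predictor would also fit the protocol's sentence.
- *That the SAP removed the adjusted analysis.* SAP 5.5 is silent on covariates, and a logistic model can be adjusted.
- *That objective (iii) is undermined.* The SAP covers the trial only. The objective concerns survivors generally, about 9,000 survey responses are expected, and the topic has its own planned article. Nothing says that SAP 5.5 replaces a survey-based analysis.
- *That the SAP dichotomises these scores throughout.* Under SAP 5.3, "Continuous secondary outcomes analyzed using paired *t*-tests and between-group comparisons of change scores". That keeps the scores intact, but it compares arms and does not estimate the association with FCR.

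Finally, the January 2025 list is headed as deviations from the SAP, so a change between protocol and SAP need not appear there. However, it does list predictor and economic analyses, which only the protocol describes. The absence of this change therefore leaves a real gap.

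**Conclusion.** The inconsistency is real and unexplained: two models for one association, with dependent variable, population and cut-offs not settled between them. In the trial-sized sample the SAP version is the less precise. The 36-66% loss is conditional on normal scores and 10-50% above the cut-off; it is not a measured property of this trial. With skewed scores and a correlation of 0.1 the range was about 5-57%. At n = 68 and an assumed correlation of 0.3, power of about 70% falls to about 30-50%.

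The size of the problem depends on the sample. At 9,000 responses the loss is immaterial for a correlation of 0.1, and shows only for very weak associations with a rare outcome. The point is therefore confined to the trial analysis. It does not touch the primary endpoint. Priority: low to moderate.

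**What to change.** In SAP sections 4 and 5.5:

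- Make linear regression using the continuous SCL4-anx, SCL6-dep, BDS checklist and Whiteley-8 scores with the FCRI score the main association analysis. Report it unadjusted and adjusted, with slope and 95% CI, and with robust standard errors if scores are skewed.
- State the population (trial or survey), the time point, which variable is dependent, and the covariates.
- Keep the cut-off-based logistic results as supplementary, and name the cut-off for each scale.
- If the logistic version has already been run, list it as a departure from the protocol's linear regression and report both.

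The cost is some SAP wording and a few lines of Stata code, with no new data. The small downside is a headline slope rather than an odds ratio; the supplementary analysis keeps the case-based reading.
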